### Treatment

After the initial P/E the first manipulation will be applied to the thoracic spine either manually or by using the Impulse iQ® (Neuromechanical Innovations, Chandler, AZ, USA) and the training program, consisting of four different exercises, will be instructed.

### Manual

For the manually performed manipulations the patient is lying supine. The therapist’s hand is under the thoracic spine using a pistol grip (the fingers are positioned with the index finger straightened and fingers 3 to 5 flexed). The patient’s forearms are crossed in front of their chest. The force is applied against the therapist’s flexed fingers, the thenar eminence and slightly cranial to the transverse process of the caudal vertebra of the treatment segment [53] (Figs. 3 and 4).

**Fig. 3 Fig3:**
[figure not shown]
Hand position. This picture shows how the hand of the therapist has to be positioned during the manual manipulation

**Fig. 4 Fig4:**
[figure not shown]
Manual manipulations. Positioning of the patient and therapist’s body during the manual manipulation

### Mechanical

For the Impulse iQ® (Neuromechanical Innovations, Chandler, AZ, USA) the patient lies prone on a treatment table, with arms next to the body, in a relaxed position. Before the treatment begins, the patient is instructed that they will hear a rattling sound that indicates the thrusts conducted by the device and a beep at the end of the treatment. The Impulse iQ® (Neuromechanical Innovations, Chandler, AZ, USA) is then put onto the vertebra that has been identified as a painful segment. A double stylus and middle force setting (peak force = 200 N), as recommended by the manufacturer for the treatment of the thoracic spine, will be used [54]. The device records and analyzes the spinal acceleration response each time a thrust is delivered using the built-in firmware. The machine then produces a series of repetitive thrusts monitoring the acceleration response and, if the response is improving, treatment continuous up to 3 s. If the acceleration response is negative (flat line or decrease) the thrust delivered by the instrument ceases (Figs. 5 and 6).

**Fig. 5 Fig5:**
[figure not shown]
Patient position during mechanical manipulation. The patient lies prone, arms next to the body in a relaxed position

**Fig. 6 Fig6:**
[figure not shown]
Positioning of the double stylus. The double stylus is positioned directly on the treatment segment

### Training program

After the first treatment session the patients will all be introduced to the home exercise program and asked to perform this program once a day for 6 weeks, while compliance with the home exercise program is assessed using a training journal:Retraining the cranio-cervical musclesTraining the holding capacity of the deep neck flexors [55]Head Lift [56]Retraining scapular muscles [55]Eye/Head coordination [55]

A detailed exercise-program may be found in Additional file 1.

### Outcomes

#### Primary outcome measure

The primary outcome measure is the VAS before and after every treatment, after 6 weeks, 3 months and 6 months. The VAS has shown to be a valid and reliable outcome measure [38–41].

The VAS tries to assess a person’s pain intensity level. The patient is asked to place a mark on a 100-mm long line with the question ‘how much pain do you have at this moment’. The beginning of the line illustrates ‘no pain’ the end of the line ‘extreme pain’. To extract the data the researcher measures the distance in millimeters between ‘no pain’ and the mark set by the participant.

#### Secondary outcome measures

Secondary outcome measures are the NDI, EQ-5D-5 L and the PGIC.

The German version of NDI is a questionnaire to assess self-rated disability in neck pain patients. It is a short paper-pencil instrument, which is based on a similar instrument used for patients with lower back pain, the Oswestry Low Back Pain Questionnaire. It consists of ten items: for example, working and driving. Each item has a score up to 5 with a total score of 50. The lower the score the less the self-rated disability [42, 43].

The EQ-5D-5 L is a valid and reliable self-report questionnaire that measures patient’s health status for clinical and economic appraisal using a descriptive system and a VAS [44, 45]. The descriptive system assesses mobility, self-care, usual activities, pain, discomfort and anxiety/depression and patients choose the most appropriate option from ‘no problem’ to ‘extreme problem’. The digits for the five dimensions can be combined in a five-digit number, which describes the health status. The VAS is vertical and 20 cm long and the endpoint options range from ‘the best health you can imagine’ to ‘the worst health you can imagine’. The participant is asked to mark the scale with a ‘X’ and write the corresponding number in a box [57].

The PGIC is a valid outcome measure that is based on a seven-point Likert scale [58]. The purpose of the PGIC is to obtain a patient’s report of their improvement over time during treatment. The scale ranges from ‘much better’, ‘better’, ‘somewhat better’, ‘no change’, ‘somewhat worse’, ‘worse’ and ‘much worse’. ‘Much better’ is rated as 7 and ‘much worse’ as 1 on the PGIC [59]. With this scale it is possible to dichotomize the participants into 2 groups; namely those that have ‘improved’ (ratings of 6 and 7) and those that have ‘not improved’ (ratings 1 to 5).

### Statistical methods

#### Number of test subjects

The sample size was calculated with the formula:$$ \mathrm{n} = \mathrm{f}\left(\upalpha, \upbeta /2\right)*2*{\upalpha}^2/{\mathrm{d}}^2 $$

Therefore: 2 × [(1.96 + 0.842)^2^ × 15^2^]/12^2^ = 24.53 [60]

The significance level alpha was chosen at 5 % and the power of 80 %.

From the literature, an expected standard deviation of 15 mm of a VAS can be determined [19]. For the expected mean difference the minimal clinically significant difference (12 mm) on the VAS was determined [61]. To be able to accomplish all needed participants, 2 patients per group will be added addressing possible withdrawals, missing data, and losses to follow up [62]. Therefore, a total of 54 patients will be recruited (27 per arm).

### Statistical analyzes

Descriptive statistics will be used to illustrate the empirical data and research population. The Shapiro-Wilk test will be used to assess whether all the variables are normally distributed. If the data is normally distributed the changes of VAS will be analyzed using analysis of variance (ANOVA) (repeated measures) to explore possible significant interaction (group x time) effects (α[1]0.05). Secondary outcome variables will be compared using the Wilcoxon test for matched pairs including confidence intervals. Participants will be sub-grouped into acute and chronic to compare the outcomes. To analyze the outcome of the PGIC, patients will be split into 2 groups (dichotomized): improved (6 and 7) and not improved (1 to 5). With the help of logistic regression, the predicted probability of the outcome will be assessed using the PGIC as dependent variables (improved/not improved). Independent variables will be age, sex, expectations, manipulation and duration of complaints. Missing data will be analyzed using an intention-to-treat method. The data will be collected, stored and analyzed in the IBM-SPSS 22 (PASW, Chicago, IL, USA) statistics program.

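### The only stated primary analysis of the VAS is conditional on Shapiro-Wilk normality tests that would fail by chance in roughly a third of trials, and the article gives no alternative

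*Protocol article*

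**What the plan says.** All the relevant rules are in the protocol article, section Statistical analyzes, except the outcome definition.

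- Pre-test: "The Shapiro-Wilk test will be used to assess whether all the variables are normally distributed".
- Condition on the primary method: "If the data is normally distributed the changes of VAS will be analyzed", by repeated-measures ANOVA, looking for a group-by-time interaction.
- The only rank method named: "Secondary outcome variables will be compared using the Wilcoxon test for matched pairs including confidence intervals".
- Primary outcome measure: "The primary outcome measure is the VAS before and after every treatment, after 6 weeks, 3 months and 6 months". Three treatments with a reading before and after each give six readings, and the three follow-ups bring the total to nine.
- Scale: "The patient is asked to place a mark on a 100-mm long line", so scores are bounded at 0 and 100.

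The article does not state the level of the Shapiro-Wilk test, whether it is run pooled or per arm, whether it is applied to raw readings or to changes, or how many rejections count as failure. It names no method for the VAS if normality is rejected.

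**The concern.** Three features combine.

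1. The condition is part of the stated rule. Whether the ANOVA is used is decided by a test on the outcome data, so the primary method cannot be known before the data are seen.
2. The tests are aimed at the variables. The normality assumption behind ANOVA concerns the model's residuals, so passing or failing on the variables does not answer the question that matters.
3. The article states no second branch for the VAS. The matched-pairs Wilcoxon test does not fill the gap: it is assigned to the secondary outcomes, and it compares values within patients, whereas the primary question compares two independent arms over time.

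At stake is the pre-specification of the primary result. If the condition fails, someone must choose between a transformation, a rank method or another model with the results available. With 27 patients per arm, that choice could decide whether the result is significant.

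**Working it through.** **Inputs from the article (Number of test subjects; Primary outcome measure).** SD 15 mm, difference 12 mm, two-sided alpha 5%, power 80%, 27 per arm, 54 in total, nine VAS readings on a 0 to 100 mm line.

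**The article's own figure.** 2 × (1.96 + 0.842)² × 15² / 12² = 24.535 (printed as 24.53), rounded up to 25; 25 + 2 = 27 per arm; 2 × 27 = 54. It reproduces, and this point does not affect it.

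**Assumptions not in the article.** Shapiro-Wilk level 5%; the condition fails if any one test rejects; the VAS means and the correlations between readings shown below.

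**Step 1: independent tests, perfectly normal data.** The chance of at least one rejection among k tests is 1 − 0.95^k.

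- Eight changes from baseline: 1 − 0.95⁸ = 0.337
- Nine readings, arms pooled: 1 − 0.95⁹ = 0.370
- Nine readings in each arm (18 tests): 1 − 0.95¹⁸ = 0.603

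**Step 2: correlated readings.** Simulated trials with n = 54, SD 15 and equal correlation between readings. Clipped means that values are held within 0 to 100. Ranges cover the settings tried and simulation error; with 1,000 runs the standard error near 35% is √(0.35 × 0.65 / 1000) ≈ 1.5 percentage points.

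| Values tested | Assumed setting | At least one rejection |
|---|---|---|
| Nine raw readings, pooled | exactly normal, correlation 0 to 0.8 | 30–39% |
| Nine raw readings, per arm | exactly normal, correlation 0 to 0.8 | 51–62% |
| Nine raw readings, pooled, clipped | means 50 to 30 mm, correlation 0 to 0.8 | 26–33% |
| Same | means 45 to 25 mm, correlation 0.5 | 37–41% |
| Same | means 40 to 20 mm, correlation 0.5 | 71–76% |
| Same | means 30 to 15 mm, correlation 0.5 | 99% |
| Eight changes from baseline, clipped | the last three mean paths | 32–36% |
| Final raw reading only, clipped | mean 25, 20, 15 mm | 13–14%, 48–49%, 92% |
| Final change only, clipped | the same three paths | 4–5% |

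**Step 3: what drives the figures.** For change scores, the floor at zero adds almost nothing, and the one-third figure is multiplicity over eight tests. For raw readings, the floor dominates once assumed means reach about 20 mm or lower, and it has little or no effect at 30 mm and above.

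**Step 4: does pre-testing inflate type I error?** One natural case was checked: a final-visit comparison of 27 against 27 with VAS clipped at 0, using a t-test if Shapiro-Wilk passes and Mann-Whitney otherwise, at means of 15, 20, 25 and 45 mm (8,000 runs each). Type I error was 4.7–4.9%, against 4.7–5.1% for the t-test used unconditionally. No inflation is visible.

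**The case against.** **The large percentages may test the wrong quantity.** The article says that changes of VAS are analysed, and for changes the floor effect nearly disappears. This stands. The sentence before it speaks of all variables, so testing raw readings is a possible reading, but the text does not settle it. The 71–99% figures need both that reading and low assumed means. It is plausible that scores fall towards zero, since Grade I and II patients are enrolled and both arms are expected to improve, but the article gives no VAS means.

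**One rejection need not void the ANOVA.** The article sets no all-or-nothing rule. If only one change score were tested, the failure rate would be the nominal 4–5%. This also stands: the one-third figure rests on reading the condition as requiring every test to pass. That the text permits such different readings is part of the defect.

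**A fallback may be stated in a document not shown.** It may, so the lack of an alternative is a statement about this article only, and a reader should not infer that the trial has no analysis for non-normal data. The objection does not reach the condition itself, which the article does fix. Naming a fallback would still leave the primary method to be selected by the outcome data.

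**Two stronger readings are tempting.** A reader might infer that the primary method will probably be chosen after the data are seen. That needs a failure rate above one half, which pooled testing reaches only for raw readings with low assumed means; testing each arm separately can also reach it, but the article does not specify that. A reader might also infer that pre-testing distorts the error rate here. The case checked shows no distortion; it does not cover an unrestricted choice of method, but nothing in the documents gives a figure for that.

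**Conclusion.** The point holds in a limited form. The article makes its only stated primary analysis conditional on normality tests of the variables and gives no alternative for the VAS. If all nine readings or all eight changes must pass at 5%, the condition fails in roughly one third of trials with perfectly normal data. It fails in about 40% to 99% if raw values are tested and assumed means fall to 25 mm or below. These figures rest on an assumed test level, an all-must-pass reading, and assumed means and correlations; only the SD, the sample size and the reading schedule come from the article.

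The conclusion is a substantial chance of a data-dependent primary method. It is not that this outcome is more likely than not, nor that type I error is inflated by a known amount. The condition also appears to buy little: in the simple two-arm case checked, the unconditional t-test held its level with scores at the floor, although that is not a test of the full repeated-measures model.

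**What to change.** Delete the normality condition and fix one primary model for the VAS before the data are analysed, keeping the group-by-time question. A repeated-measures mixed model adjusted for baseline VAS would serve, and baseline VAS is already collected. Making the stated ANOVA unconditional would also close this gap. An analysis at one time point is not proposed here, because the article names no single primary time point.

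Check residuals graphically and report what is found. Pre-specify one robustness analysis, such as a bootstrap interval or a permutation test of the arm difference, and state that it does not replace the primary result.

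The cost is about two sentences in Statistical analyzes and one extra sensitivity run. N = 54 does not change. The article reports recruitment as ongoing, so at that stage the change could still precede the analysis.

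### The stated 80% power belongs to a single 12 mm two-sample comparison, not to the planned group-by-time interaction test over nine VAS readings, none of which is named primary

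*Protocol article*

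**What the plan says.** Three sections of the Protocol article bear on this.

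- *Primary outcome measure*: "The primary outcome measure is the VAS before and after every treatment, after 6 weeks, 3 months and 6 months". The Design section sets three treatment sessions, so this makes 3 × 2 + 3 = 9 readings. None is singled out.
- *Number of test subjects*: "2 × [(1.96 + 0.842)^2^ × 15^2^]/12^2^ = 24.53", with "an expected standard deviation of 15 mm of a VAS can be determined" and "For the expected mean difference the minimal clinically significant difference (12 mm) on the VAS was determined". Error rates are given as "The significance level alpha was chosen at 5 % and the power of 80" per cent. Then "2 patients per group will be added addressing possible withdrawals, missing data, and losses to follow up", which takes 25 per arm to 27 and the total to 54. The formula contains no time point, number of measurements or within-patient correlation.
- *Statistical analyzes*: if the data are normally distributed, "the changes of VAS will be analyzed using analysis of variance (ANOVA) (repeated measures) to explore possible significant interaction (group x time) effects", at the 0.05 level. No other between-arm test of the VAS is stated.

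**The concern.** A power statement is a property of one test against one alternative. Here the sizing section describes a comparison of two means, and the analysis section describes a test of whether the between-arm difference varies over time. These are different hypotheses. The power of the second depends on the time pattern of the effect and on the within-patient correlation, and the article gives neither.

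The reading of the result is also at stake. The study aim covers both short-term and long-term outcomes. A significant interaction says only that the arms' profiles are not parallel. It does not say which arm did better, or when. Some later choice of time point would have to supply the conclusion, and the plan does not fix that choice in advance.

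**Working it through.** **Inputs from the article:** two-sided alpha 0.05, SD 15 mm, difference 12 mm, 25 per arm before the dropout allowance, nine readings.

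**Assumption, not in the article:** equal correlation ρ between any two readings on the same patient (compound symmetry), shown for ρ = 0.3, 0.5 and 0.7, with SD 15 mm at every reading.

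**1. The plan's own figure.** 2 × (1.96 + 0.842)² × 15² / 12² = 2 × 7.851 × 225 / 144 = 24.535, so 25 per arm; adding 2 gives 27, total 54. It reproduces. With 25 per arm, power for one two-sample comparison is 81% by the normal approximation and 79% by the exact t-test.

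**2. The planned test on raw VAS, baseline as one of nine time levels.** The interaction F has 8 and 48 × 8 = 384 degrees of freedom. Its noncentrality is

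λ = (n/2) × Σ(δₜ − δ̄)² / [SD² × (1 − ρ)],

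where δₜ is the between-arm difference at reading t, δ̄ is its mean over the readings, and n = 25.

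- 12 mm at all eight post-baseline readings: δ̄ = 96/9 = 10.67, and the sum is 10.67² + 8 × 1.33² = 128.
- 12 mm at one reading only: δ̄ = 12/9 = 1.33, and the sum is again 10.67² + 8 × 1.33² = 128.
- 12 mm at the three follow-ups only: δ̄ = 36/9 = 4, and the sum is 6 × 4² + 3 × 8² = 288.

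For the first two, λ = 12.5 × 128 / [225(1 − ρ)]. For the third, λ = 12.5 × 288 / [225(1 − ρ)].

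| Pattern of the 12 mm difference | ρ = 0.3 | ρ = 0.5 | ρ = 0.7 |
|---|---|---|---|
| All eight post-baseline readings | λ 10.2, 58.5% | λ 14.2, 76.3% | λ 23.7, 95.5% |
| One reading only | λ 10.2, 58.5% | λ 14.2, 76.3% | λ 23.7, 95.5% |
| Three follow-ups only | λ 22.9, 95% | λ 32.0, 99% | λ 53.3, >99% |

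Rows one and two are identical. The test responds equally to a lasting benefit and to a difference at a single reading. By the same formula, a difference confined to the three readings taken after the sessions has the power in row three.

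**3. The planned test if the response is change from baseline.** There are then eight levels. A constant 12 mm benefit gives δₜ − δ̄ = 0 throughout, so λ = 0 and the interaction test rejects at its 5% level only. The benefit would appear in the group main effect. The SD of a patient's mean change is 15 × √[(1 − ρ)(1 + 1/8)] = 13.3, 11.3 and 8.7 mm, which gives that effect about 88%, 96% and over 99% power. The plan does not name this effect as its test.

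**4. One baseline-adjusted contrast at one time point.** The residual SD is 15 × √(1 − ρ²) = 14.3, 13.0 and 10.7 mm. Then 12 / [residual SD × √(2/25)] = 2.96, 3.27 and 3.96, and power is about 83%, 89% and 97%.

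**The case against.** The best reply is that nothing here shows low power. The range in step 2 straddles 80%, and an effect confined to the follow-ups would be detected with 95% power or more. That stands. A reader might infer that the trial is underpowered, but the article gives neither the correlation nor the time pattern needed to say so.

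A reader might also infer that the test has 5% power against a lasting benefit. That needs two further steps: taking the word *changes* to mean change-from-baseline scores, and setting aside the group main effect that the same ANOVA yields. The word can equally mean change over time with the pre-treatment reading as a level, since the primary outcome counts the readings before treatment. The 5% is conditional.

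Inflated error rates from testing each reading separately, or from leaving non-sphericity uncorrected, are likewise not findings. The article plans no separate tests, and a correction is the kind of detail an analysis plan may hold. Nor does the article say how soon after each treatment the VAS is repeated.

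The article words the ANOVA as exploring the interaction, and a separate analysis plan might name a time point. Neither removes the mismatch. The test is set at 0.05 on the declared primary outcome, a formal power claim justifies the sample size, and the article itself fixes the outcome as all the readings.

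**Conclusion.** The point holds as a mismatch within the text. The sample-size arithmetic is correct, but the 80% it delivers describes a single two-sample comparison that the plan does not state. For the test it does state, power at 25 per arm runs from 58.5% to over 99% across the patterns and correlations tabulated for raw VAS. These figures rest on assumed compound symmetry, SD 15 mm at each reading and complete data. On the change-score reading, a constant benefit lies outside the interaction altogether.

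The conclusion that 80% does not apply needs none of these assumptions. It follows from setting the three sections side by side. It would be too much to say that the trial has no defined estimand: population, arms, variable and reading times are given. What is missing is the primary time point and the between-arm contrast there.

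**What to change.** Name one primary time point, at the sponsor's choice. Make the primary test the between-arm difference in VAS at that point, adjusted for baseline VAS, either by ANCOVA or as a contrast from a mixed model over all visits. Report the remaining readings and the group-by-time interaction as secondary. The SD 15 mm and 12 mm calculation then describes the test performed and is conservative for it over the correlations considered (step 4).

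If the sponsor prefers to keep the interaction as the primary test, the alternative is to size the trial for it, with the within-patient correlation and time pattern stated. That would still leave direction and timing to be settled.

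The first option costs amendment wording and no extra patients. Its downside is that only one time point carries the confirmatory claim. Recruitment is described as ongoing, so the change should be made before outcome data are examined by arm.

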**Methods/Design:**

A 6-month, randomized controlled trial consisting of 54 patients with acute or chronic neck pain patients will be conducted. Patients with no signs of major pathology and with little or no interference with daily activities will be recruited. Three treatment sessions with 4-day intervals will be carried out. The patients will be randomly assigned to receive either manually performed manipulations or electromechanical manipulations at the thoracic spine. The primary outcome is pain intensity as measured by the Visual Analogue Pain Rating Scale. The secondary outcome measures are neck physical disability using the Neck Disability Index, quality of life measured by the European Quality of Life 5 Dimensions 5 Levels and patients’ improvement using the Patient’s Global Impression of Change Scale.

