**Discussion:**

It is expected that both interventions will improve neck pain. This would be a significant finding, as thoracic spine manipulation for neck pain does not carry the same risk of injury as cervical spine manipulation. In addition, the results may provide useful information about therapeutic options for health care providers and patients for the problem of neck pain.

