### Study aim

The aim of this study is to compare the short and long-term treatment outcomes for neck pain patients using an instrument-assisted mechanical manipulation with feedback versus manual manipulations of the thoracic spine.

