### Design

There will be 3 treatment sessions and an additional training program for 6 weeks. Follow-up assessments will take place after 6 weeks, 3 months and 6 months. The 3 treatment session will always be 4 days apart. At baseline the participant will fill out the Visual Analogue Pain Rating Scale (VAS), the Neck Disability Index (NDI) and the European Quality of Life 5 Dimensions 5 Levels (EQ-5D-5 L) [38–45]. At two subsequent treatment sessions, the patient will be asked to fill out the NDI, VAS, EQ-5D-5 L, and the Patients Global Impression of Change Scale (PGIC) before the treatment [46]. The VAS will be repeated after each treatment. For the follow-up assessments the participants will receive the same questionnaires (Fig. 2).

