### Randomization

A clinician, who is not involved in the study, will independently conduct the randomization procedure. A block randomization (20 blocks of 4) using a computer-based randomization program will be conducted. The original randomization list will be stored in an opaque and sealed envelope not accessible to the therapist conducting the manipulations. Eighty sequentially numbered, sealed, opaque envelopes, containing the randomized group allocation will be prepared. At the time of treatment, these envelopes will be given to the therapist applying the manipulation, immediately prior to the execution of the manipulation. The patient will be unaware of the technique that will be applied, only that the technique may either be delivered manually or with an electromechanical instrument (Impulse iQ®, Neuromechanical Innovations, Chandler, AZ, USA). To minimize any possible effects of expectations of treatment, each participant will be asked prior to the first treatment about their expectations regarding new and conventional treatments.

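### The matched-pairs Wilcoxon test named for the secondary outcomes cannot compare two independent arms, so NDI and EQ-5D-5L have no stated manual-versus-mechanical comparison

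*Protocol article*

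**What the plan says.** The aim is a contrast between techniques: "The aim of this study is to compare the short and long-term treatment outcomes for neck pain patients using an instrument-assisted mechanical manipulation with feedback" is set against manual manipulation of the thoracic spine (Study aim). The abstract describes a parallel-group allocation: "The patients will be randomly assigned to receive either manually performed manipulations or electromechanical manipulations at the thoracic spine". The Randomization section adds: "A block randomization (20 blocks of 4) using a computer-based randomization program will be conducted". No crossover and no matching of patients is described.

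The Statistical analyzes section then assigns these methods:

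- **VAS (primary):** repeated-measures ANOVA with a group-by-time interaction.
- **Secondary outcomes:** "Secondary outcome variables will be compared using the Wilcoxon test for matched pairs including confidence intervals".
- **PGIC, in addition:** logistic regression on improved or not improved, with manipulation among the independent variables.

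The secondary outcomes are NDI, EQ-5D-5L and PGIC (Secondary outcome measures). The acute/chronic subgrouping in the same section is not a comparison of the randomised treatments.

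**The concern.** A matched-pairs test needs a natural partner for each observation. Across the arms there is none. Within a patient there is one, namely another visit of the same patient. Read as written, the sentence therefore gives a test of change over time for NDI and EQ-5D-5L, and nothing in the section supplies the missing contrast between arms.

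This matters more here than in a trial with an untreated control. Both arms receive manipulation, and the exercise programme is common to both: "After the first treatment session the patients will all be introduced to the home exercise program". Improvement within patients is likely even if the two techniques are identical, and its size cannot be attributed to either technique. At stake is whether two of the three secondary outcomes give any randomised evidence on the study question. There is also the risk that an analyst who follows the text tests each arm separately and reads significance in one arm only as a difference between techniques.

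**Working it through.** **1. How the protocol itself treats the arms.** Inputs from Number of test subjects: SD 15 mm, difference 12 mm, two-sided 5% (1.96), power 80% (0.842).

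n per arm = 2 × (1.96 + 0.842)² × 15² / 12² = 24.535. The protocol prints 24.53, so its figure is reproduced. Rounded up this is 25; 25 + 2 = 27 per arm; 2 × 27 = 54. The factor 2 belongs to the formula for two independent samples, so the protocol's own sizing treats the arms as unpaired. Blocks of 4 balance the numbers allocated and create no pairs.

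**2. What each test estimates.** Write a patient's change as c + t, where c is everything common to both arms (natural course, exercise, regression to the mean) and t is the effect of the technique.

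- Matched pairs within one arm: centre at c + t₁ or c + t₂.
- Matched pairs, arms pooled: centre at c + (t₁ + t₂)/2.
- Study aim: t₁ − t₂.

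The common part c cancels only in the third line. No version of the visit-to-visit test contains t₁ − t₂.

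**3. Illustration.** The protocol gives no NDI change or SD, so the values here are assumptions: normal changes, SD 6 points, 27 per arm, 4,000 simulated trials, two-sided 5%. Entries are the percentage of trials with a significant result.

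| Mean improvement, arm 1 / arm 2 | True difference | Matched pairs, arm 1 | Matched pairs, arm 2 | Matched pairs, pooled | Exactly one arm significant | Mann-Whitney between arms |
|---|---|---|---|---|---|---|
| 0 / 0 | 0 | 5.1 | 4.9 | 5.0 | 9.8 | 4.7 |
| 2.5 / 2.5 | 0 | 53.3 | 54.0 | 83.8 | 49.3 | 4.4 |
| 5 / 5 | 0 | 98.4 | 98.4 | >99.9 | 3.1 | 4.4 |
| 7 / 3 | 4 | >99.9 | 68.2 | >99.9 | 31.8 | 65.3 |

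Two comparisons carry the point. The 5 / 5 and 7 / 3 rows have the same average improvement of 5 points, and the pooled matched-pairs test rejects equally often in both, so it cannot tell a difference of 0 from a difference of 4. In the 2.5 / 2.5 row the techniques are identical, yet exactly one arm is significant in about half of the trials.

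**4. Which outcomes are left without a between-arm analysis.** VAS has group-by-time. PGIC has the manipulation term in the logistic model. NDI and EQ-5D-5L have only the matched-pairs test.

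**The case against.** The strongest defence is that the damage is narrow. The primary outcome keeps a between-arm analysis, the sample size rests on VAS alone, and PGIC has its own model with a treatment term. All of that stands and sets the limits of the point. It may also be that an unpaired Wilcoxon test was meant and the wrong name was written; the correction would be the same. A separate analysis plan may exist, but the protocol does not leave this method open: it fixes one that does not suit the design.

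Several stronger readings are tempting and are not supported:

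- **PGIC cannot be paired at all.** The Design section lists it at the two later treatment sessions ("and the Patients Global Impression of Change Scale (PGIC) before the treatment"), and the same questionnaires go out at follow-up. Visit-to-visit pairs exist; only a baseline value is lacking.
- **The EQ-5D-5L health-state code will be ranked.** The protocol says "The digits for the five dimensions can be combined in a five-digit number, which describes the health status". That describes the instrument; no analysis of the code is announced. The choice of index or value set can properly be left to an analysis plan.
- **The Wilcoxon results are meant to support the expected conclusion.** The abstract says "It is expected that both interventions will improve neck pain". That concerns pain, which is the primary outcome with its own group-by-time analysis, and nothing ties it to NDI or EQ-5D-5L.
- **The simulated rates are false-positive rates.** They are not. The simulated patients truly improve in those rows, so the test rejects correctly for the question it asks. The rates also vary widely with the assumed change.

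**Conclusion.** The method is wrong as written for NDI and EQ-5D-5L. The test named assesses change between visits within patients, and no manual-versus-mechanical comparison is stated for these two of the three secondary outcomes, although that comparison is the study aim. This conclusion follows from the design and needs no assumed value. The simulated figures (about 53% to 98% significant per arm with a true difference of zero) depend on an SD of 6 and improvements of 2.5 to 5 NDI points, neither of which is in the protocol, and serve only as illustration. The primary VAS analysis, the PGIC logistic model and the sample size are unaffected.

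**What to change.** Replace the sentence on the secondary outcomes with a between-arm analysis of NDI and EQ-5D-5L. Either of these would serve:

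- a baseline-adjusted ANCOVA or mixed model, reporting the manual-minus-mechanical difference with its 95% confidence interval; or
- a Mann-Whitney rank-sum test on change, with a Hodges-Lehmann estimate and interval.

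Keep PGIC in the logistic regression already planned. Report within-arm change in NDI and EQ-5D-5L descriptively, without tests offered as evidence about the techniques.

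The cost is a change of wording. It needs no new data, visits or patients, and the total stays at 54. The Trial status section reports recruitment as ongoing, so the change can be documented before analysis.
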